## 4. Clinical Outcome Definition

We will compare the surgical margin assessment in tongue cancer specimens by comparing three index tests (clinical examination, 3D ultrasound, and MRI) with the post-surgical histopathology assessments as the reference standard. 

The primary outcome will be reported as:The perioperative measurement of resection margins (mm) at five directions (Figure 1) with clinical exam and imaging compared to the post-surgical histopathology results (reference standard).The image-by-image comparison of the depth of invasion measurement (mm) from 3D ultrasound/MR imaging and histopathology slides.The depth of invasion (mm) comparison between in vivo and ex vivo ultrasound.The number of margins correctly classified as free (>5 mm), close (1–5 mm), or positive (<1 mm) margins by 3D ultrasound and MRI using histopathology findings as the reference.

The secondary outcome will be: The number of cases requiring adjuvant treatments (surgery or chemo/radiotherapy) due to T-site residuals.A change in tumor volume and resection margin measurements with 3D ultrasound imaging before and after formalin fixation.The time usage (minutes) and cost estimation for perioperative 3D ultrasound and MRI.

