## 5. Statistics

There will be three index tests used for clinical examination, 3D ultrasound imaging, and MRI of the ex vivo specimen. The reference standard will be the final histopathology result. Each case will undergo five margin measurements (anterior towards the apex of the tongue, posterior towards the base of the tongue, medial, lateral, and profound/deep margins) by three index tests and one standard reference. Tumor and specimen volume will be calculated for each case. The deep margin will be measured at equally distanced planes of imaging in every case, and the results will be correlated to the corresponding deep margin measurements from the reference standard.

The participants will be excluded from the final analysis in case of any technical issues such as non-feasibility to perform parallel slicing of the surgical specimen or patients with MRI contradictions (pacemaker, metal implants not compatible with MRI, etc.). The number of excluded participants will be reported as non-conclusive cases and will be excluded from the study.

Margin measurements (quantitative data in mm) and tumor and specimen volume measurements (quantitative data in ml) will be presented as an averaged value over two measurement repetitions, as described in Section 3.2. The measurement differences between the index tests and the reference standard will be compared by a paired *t*-test. The degree of correlation will be expressed using Pearson’s correlation coefficient, in which the index tests and the reference standard will be considered to be significantly correlated when *p* < 0.05. To evaluate the agreement between the index tests and the reference standard, we will also analyze the data using Bland–Altman plots, which show the mean difference between the two techniques with a 95% confidence interval. This allows for easy interpretation of whether the differences between the index tests and the reference standard are clinically relevant. Correlation between the plane-by-plane deep margin measurements obtained by the reference standard and the index tests will be evaluated by *t*-test, and the threshold for significance correlation will be *p* < 0.05. The correlation between the depth of invasion measurements (mm) from in vivo ultrasound and the ex vivo ultrasound will also be reported.

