The intra- and interobserver variability will be quantified by calculating the intraclass correlation coefficient (ICC). The ICC measures the reliability of the measurements between the two observers and is the measure of the degree of agreement among the observers in their assessment of margin status.

We will also classify the data into three categories of positive (<1 mm), close (between 1–5 mm), and free (>5 mm) margins. For each included case, we will compare the accuracy of each index test by computing the proportion of correctly classified margins with respect to the reference standard class. We will use the McNemar test to determine if the proportions of categories in the index tests differ significantly from those of the reference standard (paired categorical data). The results will be considered statistically significant when *p* < 0.05, with a 95% confidence interval. 

The mean time spent on delineation by the operators will be recorded and reported in minutes. Data will be analyzed with commercially available software (RStudio Team-2023). RStudio: Integrated Development for R. RStudio, Inc., Boston, MA, USA.

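### The McNemar test against histology checks for systematic over- or under-calling, not correct classification, and no named test compares correct classification between the index tests

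*Protocol article*

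**What the plan says.** Section 2 asks how accurate 3D ultrasound is compared with clinical examination and MRI.

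Section 4 lists among the primary outcomes "The number of margins correctly classified as free (>5 mm), close (1–5 mm), or positive (<1 mm) margins by 3D ultrasound and MRI", with histopathology as the reference.

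Section 5 says that "Each case will undergo five margin measurements" by each index test and the reference. It will then "classify the data into three categories of positive (<1 mm), close (between 1–5 mm), and free (>5 mm) margins". Two sentences follow on how the classes are analysed:

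- A descriptive measure: "we will compare the accuracy of each index test by computing the proportion of correctly classified margins with respect to the reference standard class".
- A significance test: "the McNemar test to determine if the proportions of categories in the index tests differ significantly from those of the reference standard".

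Section 5 then sets the threshold at p < 0.05 and mentions a 95% confidence interval in general terms, without tying the interval to the proportion correct. It names no other test for the classified data.

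**The concern.** McNemar on a table of index test by reference uses only the discordant cells and asks whether they balance. The margins on which the two methods agree do not enter the statistic. The hypothesis tested is therefore equal totals per category (marginal homogeneity), whereas the outcome is correctness margin by margin.

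Two things follow. A method that is often wrong in both directions can give a p-value near 1. A method that is nearly always right, but whose few errors run one way, can give a small p-value. The only p-value on the categorical primary outcome can thus rank methods in the opposite order to their accuracy.

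The research question is comparative, yet no named test sets the proportion correct for 3D ultrasound against that for MRI or clinical examination.

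A smaller point: the standard McNemar test is for a 2x2 table, and the plan has three ordered classes. Extensions to three categories exist, but they still do not test correctness.

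**Working it through.** **Inputs.** Five margins per case (Section 5). Section 6 plans 27 evaluable cases and 30 included, so 27 × 5 = 135 and 30 × 5 = 150 margins. The plan gives no figure for the McNemar test itself. Its sample size reproduces and is not at issue here: (1.960 + 1.282)² × (0.55 × 0.45 + 0.16 × 0.84) / 0.39² = 26.4, rounded up to 27, and 27 / 0.9 = 30.

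**Assumptions.** Two-sided alpha of 0.05; margins treated as independent; an illustrative class mix of 10% positive, 74% close and 16% free. The first two shares are from the 91-resection series in Section 1 and the third is the remainder. They are shares of cases, not of single margins, so an assumed mix of 10/35/55 was also run.

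**Formula.** With b errors one way and c the other, the exact McNemar p = min(1, 2 × P(X ≤ min(b, c))), where X ~ Binomial(b + c, ½).

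**1. Errors that cancel.** Free v not free, 150 margins, b = c = 37: p = 1.00. Correct: (150 − 74)/150 = 50.7%.

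Labels drawn at random with histology's own shares are correct in 0.10² + 0.74² + 0.16² = 58.3% of margins, or 0.10² + 0.35² + 0.55² = 43.5% under the second mix. In 4,000 simulated trials per setting (27, 30, 135 and 150 units), such a method was non-significant in about 95% to 98%, whether by exact McNemar on free v not free or by Bowker's three-category test.

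**2. Errors that run one way.**

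| Errors (b, c) | Margins | Correct | Exact p |
|---|---|---|---|
| 5, 0 | 150 | 145/150 = 96.7% | 2 × 0.5⁵ = 0.063 |
| 6, 0 | 150 | 144/150 = 96.0% | 2 × 0.5⁶ = 0.031 |
| 10, 0 | 150 | 140/150 = 93.3% | 2 × 0.5¹⁰ = 0.002 |

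Six one-way errors are the minimum for significance. If 10% of units are wrong, all in one direction, the chance of a significant result is P(at least 6 errors) under Binomial(n, 0.10):

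| Units | Chance significant |
|---|---|
| 27 | 4.7% |
| 30 | 7.3% |
| 135 | 99.4% |
| 150 | 99.8% |

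Simulation with both mixes and both tests gave 95% to 99.9% at 135–150 units and about 2% to 23% at 27–30.

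**3. What a test of correctness would do.** Cross-classify each of 150 margins as correct or incorrect for two index tests, one with 140 correct and one with 76. If correctness is independent, both are right on 140 × 76 / 150 ≈ 71. The discordant counts are 140 − 71 = 69 and 76 − 71 = 5, and exact p ≈ 2 × 10⁻¹⁵. This ignores clustering of margins within patients, which the real analysis must handle. It shows only that the test now points at the right quantity.

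**The case against.** The strongest reply is that the plan already reports accuracy. The sentence before the McNemar test computes the proportion correctly classified, so a chance-level method would show its poor figure in the results. McNemar does what its own sentence says, which is to compare category proportions. Section 5 assigns agreement to Bland–Altman plots, and a significant McNemar result is a valid sign that a method over- or under-calls. All of this stands, and it means the test need not be deleted.

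A reader might infer that the plan will declare a method accurate when p ≥ 0.05 and inaccurate when p < 0.05, so that a worthless test passes and a good one fails. The article does not support that: it states no such rule, and reading a non-significant result as agreement is a foreseeable mistake, not a stated one.

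A reader might also take the 99% figure as this trial's error rate. It needs about 135 independent margins and errors that all run one way. The unit of the McNemar test is not stated, and with one classification per case the effect is small. The percentages for random labels depend on an assumed mix, and a rejection rate near 5% is simply the nominal level when totals really are equal.

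What the reply does not answer is that the named test does not address the listed outcome and that the comparison in the research question has no test. Which three-category version to run may be left to a fuller plan. The hypothesis is written out here, and it is not the one the outcome needs.

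**Conclusion.** The point holds in this form. The only significance test named for the classified margins tests marginal homogeneity against histology, not correct classification. Accuracy is described, but with no interval or test explicitly attached, and it is not compared between index tests.

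That a chance-level method will usually be non-significant holds at every size examined, provided its category shares match those of histology. That an accurate method can be significant depends on mainly one-directional errors and on margins being the unit of analysis; it is weak at 27–30 units. The argument about what the test measures needs no assumption on class mix. The percentages are illustrations that rest on independent margins and assumed shares.

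**What to change.** - For each index test, report the proportion of margins correctly classified with a 95% confidence interval that allows for clustering within patients.
- Compare correct/incorrect between 3D ultrasound and MRI, and between 3D ultrasound and clinical examination, with a paired method that allows for five margins per case, for example a clustered McNemar test or GEE.
- If the comparison of each index test with histology is kept, use a three-category test of marginal homogeneity, label it a check for systematic over- or under-calling, and state that a non-significant result will not be read as agreement or accuracy.
- Optional: weighted kappa for the ordered classes, and sensitivity and specificity for margins of 5 mm or less, which Section 1 calls inadequate.

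The cost is a change of wording in Section 5 and some analysis code. No new data or patients are needed.

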## 6. Power Calculation and Inclusion Period

A power calculation was based on the expected change in frequency between the free margin status when diagnosed by ultrasound imaging of the surgical specimen and when evaluated using the conventional procedure in the operation theater, without using ultrasound. The sample size needed to compare two independent binomial proportions is calculated to achieve a significance level of 0.05 and 90% power. The power calculation is based on results from Koning et al. [18] that found the frequency of free margin status to be 55% using ultrasound and 16% in the conventional cohort. A 2-sample paired binary sample size calculation results in the sample size of n = 27. By estimating a 10% drop-out rate, due to technical reasons, we will aim to include 30 cases. 

In Denmark, oral cavity cancer is the second most common head and neck cancer, and it has previously been reported with an incidence of 3.5 pr. 100,000. The uptake for the Rigshospitalet Center averages more than 90 cases annually, with 1/3 being tongue tumor cases [2,49]. In Denmark, all cancer investigations and treatments take place in public hospitals, free of charge, and financed by taxes. Based on the Copenhagen oral cavity squamous cell carcinoma database [6], we expect more than 30 patients annually to be diagnosed with tongue SCC, and these are the potentially eligible participants. Some of these patients will not fulfill the inclusion criteria, and some will decline to participate in the study. Therefore, we expect to include roughly 60% of the patients over a 1.5 year period. All enrolled patients are included in the analysis, with an intention-to-treat assumption [50]. We will register the age, sex, and final pathology staging of all the eligible participants to assess the comparability of the indexed population to the recurrent general tongue cancer population.

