Following the surgery, two experienced head and neck surgeons will manually segment the tumor region on the 3D ultrasound images. This process will involve identifying and delineating the tumor boundaries based on the echogenicity differences between the tumor and the surrounding healthy tissue. Segmentation will be conducted using the ITK-SNAP segmentation software (www.itksnap.org (accessed 5 on July 2023)) [48], a widely used and validated tool for medical image segmentation. The surgeons will measure the smallest margin (anterior, posterior, lateral, medial, and deep margin). The segmentation process will be performed on approximately 10–15 equally distanced planes throughout the tumor volume. These planes will be selected to provide a comprehensive representation of the tumor and its spatial relationship with the surrounding tissue. The segmented regions from these planes will then be interpolated (using the interpolation tool in ITK-SNAP) to construct a 3D representation of the entire tumor structure. This approach allows for a detailed visualization and measurement of the tumor and its margins from multiple perspectives.

In addition to the overall tumor segmentation, the surgeons will measure the deep margin at every segmented plane. This step will provide a detailed plane-by-plane assessment of the deep margin, which is crucial for determining the adequacy of the resection. The measurements from the 3D ultrasound will then be correlated with the histopathology results to evaluate the accuracy of the ultrasound-based measurements.

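### The 90% power rests on a contrast between surgical cohorts that this accuracy study never makes, and the calculation is labelled both independent and paired

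*Protocol article*

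**What the plan says.** Section 6 (Power Calculation and Inclusion Period) opens by basing power on a change in free-margin frequency between ultrasound imaging of the specimen and the conventional theatre procedure. It continues: "The sample size needed to compare two independent binomial proportions is calculated to achieve a significance level of 0.05 and 90% power". The rates come from a cited study that "found the frequency of free margin status to be 55% using ultrasound and 16% in the conventional cohort". The section then states: "A 2-sample paired binary sample size calculation results in the sample size of" 27, and raises this to 30 for 10% drop-out.

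The rest of the article describes a different design:

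- **Source of the rates.** Section 1 describes the same cited study as one in which ultrasound-guided resection improved margin status and halved adjuvant radiotherapy.
- **Groups.** Sections 3 and 5 describe one cohort, with three index tests and one histopathology reference for every case.
- **Timing.** Section 3.2.2: "Following the surgery, two experienced head and neck surgeons will manually segment the tumor region on the 3D ultrasound images".
- **Primary outcomes (section 4).** Margins in mm against histopathology, depth of invasion, and the number of margins correctly classified as free, close or positive.
- **Tests (section 5).** Paired t-test, Pearson correlation, Bland–Altman, intraclass correlation, and McNemar for each index test against histopathology.

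**The concern.** A power figure has meaning only for a named contrast and a named test. The 55% and 16% describe how often surgery achieved a free margin in two cohorts operated on in different ways. This study has no second way of operating, so it has no such pair of rates to compare.

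The section also names two incompatible designs within a few lines. Independent groups need 27 in each of two groups, while a paired design needs 27 specimens and depends on how often the two readings disagree. A reader cannot tell which calculation was done.

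The 90% is the only statement of what 30 cases can deliver. Section 8 says the trial explores whether 3D ultrasound has a higher diagnostic rate than MRI and clinical examination. A reader could take the study to have been sized for that question, and it was not.

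**Working it through.** **Inputs.** From section 6: rates 0.55 and 0.16 (difference 0.39), alpha 0.05, power 90%, n = 27, drop-out 10%. Sidedness is not stated; two-sided is assumed unless noted (z = 1.960 and 1.282). No discordance between paired readings is given, so its whole possible range is used.

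**1. The plan's own figure.** Two independent proportions, unpooled variance:

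n per group = (1.960 + 1.282)² × (0.55 × 0.45 + 0.16 × 0.84) / 0.39² = 26.4, so 27 per group and 54 in total.

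Drop-out: 27 / (1 − 0.10) = 30, as stated. Other versions of the independent-groups formula give 30 per group (pooled) or 35 (pooled with continuity correction).

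**2. The same rates in a paired design.** Let p10 be the proportion free by the first method only, p01 the proportion free by the second only, ψ = p10 + p01 and d = p10 − p01 = 0.39. McNemar sample size:

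n = (1.960 √ψ + 1.282 √(ψ − d²))² / d²

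| Assumption | p10 | p01 | ψ | n for 90% | Exact power, 27 pairs |
|---|---|---|---|---|---|
| No reverse discordance (minimum) | 0.39 | 0 | 0.39 | 22.5 → 23 | 98% |
| 3% reverse discordance | 0.42 | 0.03 | 0.45 | 26.7 → 27 | 90% |
| Independent readings | 0.462 | 0.072 | 0.534 | 32.5 → 33 | 79% |
| Maximum discordance | 0.55 | 0.16 | 0.71 | 44.7 → 45 | 63% |

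A one-sided McNemar calculation with independent readings gives 26.1, also 27. So 27 can arise from a paired formula, but only with an assumption that the article does not state.

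**3. Does any planned analysis use this contrast?** The outcomes are agreement in mm, depth of invasion and correct classification. The only test named for the categories compares each index test with histopathology. None compares free-margin rates between guided and conventional surgery, and none can, because each specimen has one resection and one histology result.

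**4. What 27 evaluable patients do deliver.** With 5 margins each there are 27 × 5 = 135 margins. Taking 80% correctly classified as an illustration (the article gives no accuracy rate), the 95% CI half-width is:

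- margins independent: 1.96 √(0.8 × 0.2 / 135) = 0.067, about ±7 points;
- margins fully clustered within patient: 1.96 √(0.8 × 0.2 / 27) = 0.151, about ±15 points.

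For a Bland–Altman limit of agreement in one direction, with one value per patient: 1.96 × SD × √(3/27) = ±0.65 SD.

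**The case against.** **The opening sentence of section 6 can be read as ultrasound readings against the surgeon's readings of the same specimens, which this study does have.** That reading makes the paired label sensible. It does not rescue the figure: 55% and 16% are not two readings of one specimen, a higher rate of calling margins free is not accuracy, and the planned McNemar test is against histopathology.

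**The article condenses a fuller protocol, where the discordance may be given.** This stands as far as it goes: the missing discordance alone is not a finding. The conflict between two named designs, and the source of the rates, are in the text as printed.

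**A reader might infer that 27 is certainly a per-group number and that the study is half the size it needs.** The match with 26.4 is strong, and section 6 itself names independent proportions. But no formula or sidedness is stated, and a paired 27 is possible as shown. The per-group origin is indicated, not proven.

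**A reader might also infer an accrual shortfall**, since section 6 says "we expect to include roughly 60% of the patients over a 1.5 year period" and 30 × 1.5 × 0.6 = 27, below the target of 30. The text says more than 30 patients a year, so 27 is a floor. At 30 / (1.5 × 0.6) = 33.3 a year the target is met, which fits that wording.

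**Finally, a reader might infer that the study is underpowered for ultrasound against MRI or clinical examination.** The article gives no accuracy rates and specifies no head-to-head test. On an assumed 80% against 60% correct at patient level, exact power with 27 patients would be about 25% with independent errors and 46% with no reverse discordance. These are illustrations and do not measure the defect.

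**Conclusion.** The point holds in two parts. First, the stated 90% power describes a treatment contrast between surgical cohorts and applies to no outcome in section 4 and no test in section 5. This follows from the article's own account of the cited study and of its own design, and needs no calculation. Second, section 6 calls one calculation both independent and paired, and these are not interchangeable: 27 per group (54 in total) by the unpooled independent formula, against 23 to 45 pairs by two-sided McNemar. Read as paired, the true power with 27 specimens would lie anywhere between 98% and 63%, and at 79% if the readings were independent. These ranges assume a two-sided 5% test and the article's own 55% and 16%.

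This does not show that 30 patients are too few for a study of agreement and accuracy. It shows that the number has not been justified for that purpose.

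**What to change.** In section 6:

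1. Withdraw the 90% power claim for this study and delete the description as two independent proportions.
2. Keep 30 enrolled and 27 evaluable, and justify the number by precision of the actual outcomes. For the proportion of margins correctly classified, state the expected 95% CI half-width per margin, allowing for five margins per patient: at 80% correct, between about ±7 points (135 independent margins) and about ±15 points (fully clustered), with the assumed within-patient correlation. For Bland–Altman, state about ±0.65 SD for each limit, one direction at a time.
3. Optionally, give the paired difference in proportion correct between 3D ultrasound and each comparator that 27 patients could detect, over a stated range of discordance.

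The accrual text needs no change on this account. The cost is the rewording of one section and a less favourable statement about power. No patients or procedures are added.
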